### Outcomes and measurements

#### Primary outcomes

The primary outcome of the study will be LFCN injury. Nerve injury will be assessed 3 months after the surgery during an outpatient visit using a patient-based questionnaire. Based on previous studies, we defined LFCN injury as having (1) no sensation, (2) numbness, (3) tingling, or (4) pain in the lateral aspect of the thigh except at the site of the wound [12].

#### Secondary outcomes

The secondary outcome will be assessed based on patient-reported outcomes (PROs) at 3 months after surgery in an outpatient setting to examine the extent to which LFCN injury has affected the patient’s quality of life (QOL) and complications (dislocations, infections, or intraoperative and periprosthetic fracture).

PROs will be evaluated using the Western Ontario and McMaster Universities Osteoarthritis Index (WOMAC) (pain, stiffness, and function subscales), the Japanese Orthopaedic Association Hip-disease Evaluation Questionnaire (JHEQ), and the Forgotten-Joint Score-12 (FJS-12).

The WOMAC was first described by Bellamy and Buchanan in 1986. It uses a scoring system with a total score of 0 (poor) to 96 (excellent) and has since been used worldwide to evaluate hip and knee osteoarthritis. The JHEQ is a self-administered questionnaire for evaluating hip disorders in the Japanese population with a total score of 0 (poor) to 84 (excellent). The FJS-12 is a self-administered questionnaire measuring the PROs on the ability of the patient to forget about their prosthetic implant in everyday life and has a total score of between 0 (poor) and 84 (excellent) [26]. The lowest and highest scores for WOMAC are 0 and 96, whereas those of JHEQ are 0 and 84; thus, the lowest and highest scores for each questionnaire will be converted to 0 and 100.

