**Methods:**

We will conduct a prospective, randomized, controlled study. All patients will be divided into a fan variation and a non-fan variation group using ultrasonography before surgery. Patients with non-fan variation LFCN will receive conventional fasciotomy and lateral fasciotomy in the order specified in the allocation table created in advance by our clinical trial center. The primary endpoint will be the presence of LFCN injury during an outpatient visit using a patient-based questionnaire. The secondary endpoints will be assessed based on patient-reported outcomes at 3 months after surgery in an outpatient setting using the Western Ontario and McMaster Universities Osteoarthritis Index, the Japanese Orthopaedic Association Hip-disease Evaluation Questionnaire, and the Forgotten-Joint Score-12.

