### Study timeline and data collection

After providing consent, study subjects will participate in the study for a total of 4 months, consisting of a 1-month pre-observation period and a 3-month post-observation period. The timeline for the assessment and data collection regarding primary and secondary outcomes is shown in Fig. 2.

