**Fig. 2 Fig2:**
[figure not shown]
The schedule of enrolment, intervention, and assessments. WOMAC, Western Ontario and McMaster Universities Osteoarthritis Index; JHEQ, Japanese Orthopaedic Association Hip-disease Evaluation Questionnaire; FJS-12, Forgotten-Joint Score-12

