### Statistical analysis

Chi-square test will be used to compare the presence of LFCN injury. We will perform a normality test using Shapiro-Wilk to detect parametric or nonparametric data. To assess the effect of LFCN injury on patient QOL to compare differences in the PRO assessments between lateral and conventional approach, the Mann-Whitney *U* test will be used if data is non-parametric, and the *t*-test will be used if data is parametric.

*P* < 0.05 will be considered significant. We will also present treatment effects and confidence intervals and perform adjusting for confounding factors as an exploratory analysis using logistic regression or multiple regression. Statistical analyses will be performed using SPSS software version 22 for Mac (IBM Corp., Armonk, NY, USA).

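### The main between-arm comparison of WOMAC and JHEQ uses unadjusted 3-month scores and names no preoperative score, which gives up precision

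*Protocol article*

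**What the plan says.** The Secondary outcomes section of the protocol article places the patient-reported outcomes at one time point: "The secondary outcome will be assessed based on patient-reported outcomes (PROs) at 3 months after surgery in an outpatient setting". The Methods paragraph of the Abstract agrees: "The secondary endpoints will be assessed based on patient-reported outcomes at 3 months after surgery in an outpatient setting". The instruments are WOMAC (with pain, stiffness and function subscales), JHEQ and FJS-12.

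The Study timeline and data collection section describes four months of participation, "consisting of a 1-month pre-observation period and a 3-month post-observation period". For the assessment times it refers to a figure: "The timeline for the assessment and data collection regarding primary and secondary outcomes is shown in Fig. 2". That figure is not shown in the text at hand. Its legend spells out all three instruments, so they appear in the schedule, but the visits at which they are collected cannot be read.

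The Statistical analysis section states the purpose of the test as "to compare differences in the PRO assessments between lateral and conventional approach". The choice of test follows a Shapiro-Wilk check: "the Mann-Whitney *U* test will be used if data is non-parametric, and the *t*-test will be used if data is parametric". The section adds effect estimates, confidence intervals and an exploratory regression adjustment for confounding factors that it does not name.

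**The concern.** WOMAC and JHEQ rate the hip itself, so a patient can complete them before the operation. To the extent that the score before surgery predicts the score at 3 months, a comparison that ignores it leaves explainable variation in the error term. The arm difference is then estimated less precisely than the same patients would allow. A chance difference in preoperative severity between the arms also passes partly into the 3-month result.

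This is a choice stated in the article, not a detail it leaves open. The main test is specified and has no baseline term, while adjustment is given exploratory status. A baseline-adjusted main analysis introduced later would depart from the published plan. The outcome is secondary, so the trial's main conclusion is not at stake.

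**Working it through.** **Inputs from the protocol article**
- Arms randomised 1:1 (Study setting).
- Enrolment of 72 per arm in the first Sample size section and 144 per arm in the second. The two disagree; both are carried through here.
- Two-sided 5% level (Statistical analysis).
- Injury rates of 28.6% versus 10% (first Sample size section) or 28.6% versus 15% (second).

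**Inputs not in the document**
- The correlation r between the preoperative and 3-month score. Assumed range 0.3 to 0.6.
- No standard deviation, target difference or power is stated for any patient-reported outcome, so there is no stated figure to reproduce. Results are in SD units; the linear conversion to 0–100 does not alter them.

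**1. Is the unadjusted comparison valid?** A simulation of the t-test with no true effect (65 per arm, 20,000 runs) gave a mean difference of about 0 and a type I error of 0.049 to 0.050 for correlations from 0 to 0.7. Omitting the baseline therefore does not bias the randomised comparison or disturb its level.

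**2. Precision given up.** Variance of the ANCOVA arm difference relative to the unadjusted one = 1 − r².

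| r | 1 − r² | variance cut | equivalent sample, 1/(1 − r²) |
|---|---|---|---|
| 0.3 | 0.91 | 9% | 1.10 |
| 0.5 | 0.75 | 25% | 1.33 |
| 0.6 | 0.64 | 36% | 1.56 |

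**3. Difference detectable with 80% power.** Unadjusted: (1.960 + 0.842) × √(2/n). Adjusted: the same × √(1 − r²).
- n = 72: 2.802 × 0.167 = 0.47 SD; adjusted 0.45, 0.40 and 0.37 SD at r = 0.3, 0.5 and 0.6.
- n = 144: 2.802 × 0.118 = 0.33 SD; adjusted 0.31, 0.29 and 0.26 SD.

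**4. Exposure to chance imbalance.** Standard error of the baseline difference = √(2/n): 0.167 SD at 72 per arm, 0.118 SD at 144. An imbalance of one standard error carries r × √(2/n) into the 3-month difference.
- n = 72: 0.05, 0.08 and 0.10 SD at r = 0.3, 0.5 and 0.6.
- n = 144: 0.04, 0.06 and 0.07 SD.

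In the simulation at r = 0.5, trials with an imbalance above one standard error had a type I error of 0.090 and the others 0.031. These average to about 5%.

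**5. Scale of a plausible arm difference.** Suppose the arms differ on these scores only through nerve injury, and injury costs 0.5 SD (assumed). The arm difference is then 0.186 × 0.5 = 0.09 SD under the first pair of rates and 0.136 × 0.5 = 0.07 SD under the second. That is of the same order as the carry-over in step 4, and well below the detectable differences in step 3 even after adjustment.

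**6. Incomplete baselines.** If only a fraction f of patients has a baseline and the rest receive the mean, the variance factor is about 1 − f·r². With f = 0.5 (assumed), the cut is 0.5 × 0.09 = 4.5% to 0.5 × 0.36 = 18%.

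Steps 2, 3 and 6 describe a difference in means. They do not transfer exactly to the Mann-Whitney branch.

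**The case against.** Three stronger readings are tempting, and the document supports none of them.

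- **That the scores are collected only at 3 months.** The schedule sits in Fig. 2, whose columns cannot be seen here. Stating when an endpoint is assessed does not exclude a preoperative measurement. What can be said is that the stated endpoint and main test use no preoperative score.
- **That preoperative differences will pass as effects of the operation.** Both arms have the same operation apart from the fasciotomy site, and no before-to-after effect is planned. Under randomisation, baseline differences are chance and the 5% level already allows for them, as step 1 shows.
- **That the effect of nerve injury on quality of life will be confounded by preoperative status.** Injured and uninjured patients are indeed not randomised groups, and the article gives that effect as a purpose of these outcomes. The test it specifies, however, contrasts the randomised arms. The mismatch between aim and contrast is a separate matter, and ANCOVA between arms would not resolve it.

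It can also be said that adjustment is already planned and that a covariate list is commonly left to the analysis plan. That is fair for the list. It does not answer the point that the article makes the unadjusted test the main comparison.

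The remaining objections concern size and cost, and they stand. The correlation is assumed. The first participant was enrolled in June 2019, the article appeared in July 2022, and completion is scheduled for March 2023. If baselines were never taken, many cannot be recovered. The timeline also names a preoperative period, not a specific visit.

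**Conclusion.** The point holds as a question of efficiency on a secondary outcome. The planned comparison of WOMAC and JHEQ is unbiased and keeps its 5% level. It is less precise than one adjusted for the preoperative score: the variance is 9% to 36% higher than need be when expressed as the cut that adjustment would bring, at an assumed correlation of 0.3 to 0.6. It also leaves the result exposed to chance imbalance with a standard error of 0.167 SD at 72 per arm or 0.118 SD at 144. Adjustment would not by itself make a difference of 0.07 to 0.09 SD detectable. Its value is a narrower confidence interval and protection against an unlucky allocation. The change is worth making because it costs little, but the size of the gain depends on a correlation that the document does not give and on how many patients have a preoperative score.

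**What to change.** In the Statistical analysis section, make the main WOMAC and JHEQ comparison the 3-month score adjusted for its own preoperative score by ANCOVA, and report the adjusted arm difference with its confidence interval. Keep FJS-12 as a 3-month comparison only, since it asks about the implant and has no preoperative counterpart.

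State in the text whether preoperative WOMAC and JHEQ are collected.
- If Fig. 2 already schedules them, only the analysis sentence changes.
- If not, collect both questionnaires in the pre-observation period, before allocation, from the patients still to be enrolled. Keep patients without a baseline in the randomised comparison by mean imputation or a missing-baseline indicator instead of excluding them. This device suits the comparison of randomised arms, not a comparison of injured with uninjured patients.

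The cost is one analysis sentence and, where needed, two self-completed questionnaires per remaining patient. The downsides are slight questionnaire burden and a smaller precision gain where baselines are missing. If recruitment has ended, only scores already collected can be used.

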### Sample size

According to previous studies, the incidence of LFCN injury due to THA with the DAA is 28.6% in non-fan variation patients [16]. Therefore, we hypothesize the lateral DAA approach will reduce the rate of LFCN injury to 15%. Using an alpha of 5% and a power of 80% in two-tailed analysis, 130 subjects need to be recruited. These calculations were performed using SAS software version 9.4 (SAS Institute, Cary, NC, USA). As we expect a 10% dropout rate, we will enroll a minimum of 144 patients in each group.

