## Methods

### Study setting

This is a dual-center, double-blind, prospective randomized controlled two-arm trial with parallel group design in a 1:1 allocation ratio. The study is conducted in the Juntendo University Hospital and the Juntendo Tokyo Koto Geriatric Medical Center in Japan.

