### Sample size

A sample size of 144 subjects is planned. According to our previous study, the overall incidence of LFCN injury incidence after DAA for THA is 42%, and the incidence of non-fan variation is 28.6% [16]. Thus, we hypothesize the lateral DAA approach will reduce the rate of LFCN injury to 10%. Using an alpha error of 5% and a power of 80% in two-tailed analysis, 124 subjects need to be recruited. These calculations were performed using SAS software version 9.4 (SAS Institute, Cary, NC, USA). Considering the dropout, we will enroll a minimum of 72 patients in each group.

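### 130 subjects do not give 80% power for 28.6% versus 15%: power is about 76% if 130 is per group and 47% if it is the total

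*Protocol article*

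**What the plan says.** The protocol article has two sections headed Sample size. This point concerns the second one, which follows the secondary outcomes.

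- Control rate: "the incidence of LFCN injury due to THA with the DAA is 28.6% in non-fan variation patients".
- Target rate: "we hypothesize the lateral DAA approach will reduce the rate of LFCN injury to 15" per cent.
- Result: "Using an alpha of 5% and a power of 80% in two-tailed analysis, 130 subjects need to be recruited". Whether this is a total or a per-group number is not stated.
- Enrolment: "As we expect a 10% dropout rate, we will enroll a minimum of 144 patients in each group".

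The other design features needed are given elsewhere. Study setting describes a "parallel group design in a 1:1 allocation ratio", and Statistical analysis says that a "Chi-square test will be used to compare the presence of LFCN injury".

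The first Sample size section, after the eligibility criteria, uses a 10% target rate and gives a different scale of enrolment: "A sample size of 144 subjects is planned", and "we will enroll a minimum of 72 patients in each group".

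**The concern.** A fall from 28.6% to 15% is a difference of 13.6 percentage points. At 80% power that needs clearly more than 65 patients per group, and also somewhat more than 130 per group, so the stated number looked wrong on either reading. The dropout step looked wrong too: 144 per group is close to what the comparison needs before anyone is lost.

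What is at stake is the power claim for the primary endpoint. If the trial runs at 144 patients in all, it is about as likely to miss a true reduction to 15% as to find it. A non-significant result would still be read against a claimed power of 80%.

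**Working it through.** **Inputs.** p1 = 0.286, p2 = 0.15, two-sided alpha 5% (z = 1.96), power 80% (z = 0.8416) and 10% dropout, all from the second Sample size section. Allocation is 1:1 (Study setting) and the test is chi-square (Statistical analysis). The difference is 0.136 and the mean rate is 0.218.

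**Trying to reproduce 130.** The formula matching an uncorrected chi-square test is

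n per group = [1.96 × √(2 × 0.218 × 0.782) + 0.8416 × √(0.286 × 0.714 + 0.15 × 0.85)]² / 0.136²

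= [1.96 × 0.5839 + 0.8416 × 0.5759]² / 0.018496 = (1.1445 + 0.4847)² / 0.018496 = 143.5, so 144 per group and 288 in total.

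Other formulas for the same inputs:

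| Method | n per group, two-sided | n per group, one-sided |
|---|---|---|
| Pooled/unpooled (above) | 144 | 113 |
| Unpooled variance | 141 | 111 |
| Arcsine | 142 | 112 |
| Pooled variance only | 145 | 114 |
| Log odds ratio | 149 | 118 |
| Continuity-corrected | 158 | 128 |

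No two-sided method gives 130 per group, and every two-sided total is 282 or more. Only the one-sided, continuity-corrected version comes near 130, and the section specifies a two-tailed analysis.

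**Power at the stated number.** Power = Φ{[0.136 × √n − 1.1445] / 0.5759}, with n per group.

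| n per group | Corresponds to | Power | Exact, uncorrected chi-square |
|---|---|---|---|
| 65 | 130 in total | 46.7% | 47.1% |
| 72 | 144 in total, no dropout | 50.7% | not run |
| 130 | 130 per group | 76.0% | 76.5% |
| 144 | 144 per group, no dropout | 80.1% | 80.8% |

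For example, at n = 130: (0.136 × 11.402 − 1.1445) / 0.5759 = 0.705, and Φ(0.705) = 0.760. With a continuity-corrected chi-square test, exact power is lower: 39.1% at 65 and 71.9% at 130 per group.

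**The dropout step.** 130 / 0.9 = 144.4, so the 144 was evidently built from 130. In the other direction, 144 × 0.9 = 129.6, so about 130 per group remain and power is 76%. Starting from the correct 144 evaluable, 144 / 0.9 = 160 enrolled per group, 320 in total.

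**What the stated numbers can detect.** Holding the control rate at 28.6%, 80% power is reached at a lateral rate of about 14.4% with 130 per group, and about 9.5% with 65 per group.

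**The case against.** The arithmetic is not in dispute; the case on the other side is about size.

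First, the section moves from 130, through 10% dropout, to 144 in each group, so its own wording points to 130 per group. The 47% figure arises only by bringing in the total of 144 from the first Sample size section, which is a different calculation with a 10% target. That is fair, and the per-group reading is the more natural one within this section. It does not remove the other reading: 130 is never labelled, 130 / 0.9 gives 144 just as well as a total, and the first section plans 144 patients in all.

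Second, on the per-group reading the shortfall is 4 points of power, and the calculation is sensitive to the control rate. With the same formula, a control rate of 29.4% instead of 28.6% would give 130 per group. This shows that the error is modest on that reading. It does not make the statement correct, because the section says 28.6%.

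Third, 144 is given as a minimum, and 144 evaluable per group would give 80.1%. So enrolment meets the requirement before attrition; what is missing is the margin for the dropout that the section itself expects.

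Fourth, the conflict between the two Sample size sections is arguably the larger problem. It is a separate one: choosing the second section over the first would still leave a number that does not follow from its inputs.

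**Conclusion.** The concern holds. With 28.6% versus 15%, two-sided 5%, 1:1 allocation and a chi-square test, 80% power needs 144 evaluable patients per group, and 130 is neither that figure nor the total of 288. Power is about 76% if 130 is per group, a shortfall of 4 points, and about 47% if it is the total, a shortfall of 33 points. The enrolment target of 144 per group carries no dropout allowance. At the assumed 10% loss, it too delivers 76%.

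The failure to reach 130 does not depend on which two-sided formula is used. How serious it is depends on which enrolment figure is operative, and the protocol article leaves that open. Because the claimed 80% fails on both readings and concerns the primary endpoint, the statement must be corrected.

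**What to change.** Decide which enrolment figure governs the trial, reconcile the two Sample size sections to it, and label every number as total or per group. Then replace the power statement with one of these:

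- **144 per group kept:** 144 enrolled per group, about 130 evaluable after 10% dropout, give 76% power for 28.6% versus 15%, and 80% power for a lateral rate of 14.4%.
- **144 in total kept:** remove the 15% scenario, or state its power as about 47% after 10% dropout. If the 15% scenario is removed, the first section's figure of 124 also needs recalculating, because 28.6% versus 10% needs 70 evaluable per group by the same formula, and 62 per group gives about 75%.
- **80% power at 15% wanted:** 144 evaluable and 160 enrolled per group.

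The first two options change wording only. They cost no patients, but the stated power falls. The third needs 16 more patients per group than the second section plans (160 − 144), or 176 more in total than the first section plans (320 − 144).

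### Two current sample-size sections contradict each other (10% vs 15% lateral-arm rate, 72 vs 144 per group), and neither number needed follows from its own inputs

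*Protocol article*

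**What the plan says.** The Methods of the protocol article carry two sections with the heading Sample size, one after Eligibility criteria and one after Outcomes and measurements. Neither is marked as superseded.

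- **First section.** It opens with "A sample size of 144 subjects is planned". It takes a non-fan injury rate of 28.6% as the control rate and states that "we hypothesize the lateral DAA approach will reduce the rate of LFCN injury to 10" per cent. It continues: "Using an alpha error of 5% and a power of 80% in two-tailed analysis, 124 subjects need to be recruited". Enrolment is then set: "Considering the dropout, we will enroll a minimum of 72 patients in each group". No dropout rate is given.
- **Second section.** It starts from the same control rate ("the incidence of LFCN injury due to THA with the DAA is 28.6% in non-fan variation patients") but states that "we hypothesize the lateral DAA approach will reduce the rate of LFCN injury to 15" per cent. With the same alpha, sidedness and power it arrives at 130 subjects, and closes: "As we expect a 10% dropout rate, we will enroll a minimum of 144 patients in each group".

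Study setting fixes 1:1 allocation, and Statistical analysis names the chi-square test for the primary outcome. Trial status describes the protocol as a single version 1.0.

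**The concern.** The two sections agree on the control rate, alpha, sidedness and nominal power. They disagree on the lateral-arm rate, the number needed and the number enrolled per group. The number 144 is a total in one and a per-group figure in the other, so the enrolment target differs two-fold (144 or 288 patients).

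There is a second fault beneath the contradiction. If the numbers needed do not follow from the stated inputs, deleting either section would still leave a wrong number in the one that survives. At stake are when enrolment is complete, which difference the trial was designed to detect, and whether the quoted 80% power is true of any design on the page.

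**Working it through.** **Inputs.** Control rate p1 = 0.286 (both sections). Lateral-arm rate p2 = 0.10 (first) or 0.15 (second). Two-sided alpha 5%, so z = 1.960; power 80%, so z = 0.842. Allocation 1:1.

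**Step 1: try to reproduce the numbers needed.** The pooled formula, which matches an uncorrected chi-square test, is

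n per group = [1.960·√(2·p̄·(1−p̄)) + 0.842·√(p1(1−p1) + p2(1−p2))]² / (p1−p2)², with p̄ = (p1+p2)/2.

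- For 10%: p̄ = 0.193; [1.960·√0.3115 + 0.842·√0.2942]² / 0.186² = 2.404 / 0.03460 = 69.5, so 70 per group, 140 in total. The section says 124.
- For 15%: p̄ = 0.218; [1.960·√0.3410 + 0.842·√0.3317]² / 0.136² = 2.654 / 0.01850 = 143.5, so 144 per group, 288 in total. The section says 130.

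Other common variants, per group:

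| Method | 10% | 15% |
|---|---|---|
| Two-sided, pooled | 70 | 144 |
| Two-sided, unpooled or arcsine | 67 | 141-142 |
| Two-sided, continuity-corrected | 80 | 158 |
| One-sided, pooled | 55 | 113 |
| One-sided, continuity-corrected | 65 | 128 |

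None gives 124 in total for 10%. No two-sided variant gives 130 for 15%, either as a total or per group. The nearest value for 15% is the one-sided corrected 128 per group, but the section says two-tailed.

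**Step 2: the dropout step.** Second section: 130 / 0.9 = 144.4, so 144 is 130 inflated for 10% dropout if both are totals. First section: 1 − 124/144 = 0.139, so its own figures imply about 14% dropout, a rate it does not state.

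**Step 3: achieved power.** Power ≈ Φ{[(p1−p2)·√n − 1.960·√(2·p̄·(1−p̄))] / √(p1(1−p1) + p2(1−p2))}. The lower figure in each range is this approximation; the upper is exact enumeration of the uncorrected chi-square test.

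| Per group | Origin | Power, 28.6% vs 10% | Power, 28.6% vs 15% |
|---|---|---|---|
| 62 | first section's own 124 | 75-76% | 45% |
| 65 | 72 less 10% dropout (rate taken from the second section) | 77-78% | 47% |
| 72 | first section, enrolled | 81-83% | 51-52% |
| 130 | 144 less 10% dropout | 97% | 76% |
| 144 | second section, enrolled | 98% | 80-81% |

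So the first section reaches 80% for its 10% target only if nobody drops out, and the second reaches 80% for its 15% target only on the same condition.

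**The case against.** The strongest defence is that the words about each group in the second section are a slip, and that 144 in total was always meant. The dropout arithmetic supports this (130 / 0.9 is about 144), and the first section plans the same total. A reader might therefore treat the slip as established. The document does not go that far, because 144 per group is also exactly the pooled two-sided requirement for 28.6% vs 15% before dropout. Both readings are open. Even if the slip is granted, it removes only the two-fold enrolment conflict: 10% vs 15% and 124 vs 130 remain, and the 15% target would then have about 50% power.

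A reader might also infer more than the text supports:

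- *That a null result could not be interpreted.* Statistical analysis promises treatment effects with confidence intervals, and the interval can be read whatever difference was planned.
- *That the size could be chosen once results are known.* No interim look is described, and Blinding covers the statistician, data analyst and follow-up observer. This is a theoretical risk, not something the document shows.
- *That the stated power differs.* Both sections state 80%; only the achieved power differs.
- *That the chance of success for 15% is half of what is claimed.* At 65 to 72 per group it is 47-52% against 80%, roughly 60-65% of the claim.

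It is also fair to note that both enrolment figures are given as minimums. That softens the stopping point but not the conflict, since the first section also gives 144 as the planned size.

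**Conclusion.** The point stands. The article gives two incompatible target rates, numbers needed and enrolment figures, and nothing in it says which governs. The numbers needed are too low for their stated inputs: 124 against 140 in total for 10%, and 130 against 288 in total for 15% (or 130 against 144 if 130 was meant per group). Once dropout is allowed for, neither section delivers its stated 80%: 75-78% for 10% under the first, 76% for 15% under the second. If 144 in total is the real size, power for 15% is 47% after 10% dropout.

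These figures rest on the 28.6% control rate, 1:1 allocation and an uncorrected chi-square test. The 65 and 130 per group also rest on the 10% dropout rate, which only the second section states; the first section's own figures imply about 14%.

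**What to change.** Replace both sections with one statement giving one control rate, one lateral-arm rate, one dropout rate, and one evaluable and one enrolled number per group. Redo the calculation and restate the achieved power. Deleting one section without recalculating is not enough. Record the change as a dated amendment before unblinding. Suggested wording, according to what was meant:

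- If 144 in total: *72 per group enrolled, about 65 evaluable after 10% dropout; power about 77% for 28.6% vs 10% and about 47% for 28.6% vs 15%.*
- If 144 per group: *144 per group enrolled, about 130 evaluable after 10% dropout; power about 76% for 28.6% vs 15%.*

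The cost is a wording amendment and a less favourable stated power. No extra patients are needed provided that power is accepted. Holding a true 80% after 10% dropout would take 70 / 0.9, so 78 per group (156 in total) for 10%, or 144 / 0.9 = 160 per group (320 in total) for 15%.
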